**Results:**

The study started in December 2013 and patient recruitment is programed until October 2015. The expected results are that vildagliptin will improve the endothelial function in patients with T2DM and hypertension compared to glibenclamide treatment, independently of glycemic control.

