## Randomization and follow-up

After screening for eligibility, 50 individuals will be submitted to an evaluation of endothelial function using the Endo-PAT 2000 device and measurement of the arterial stiffness by applanation tonometry of radial artery. Subsequently, they will be randomly allocated to the two arms of the study: Group 1 will receive vildagliptin (100 mg/day b.i.d.) added-on to metformin (500–2550 mg/day according to glycemic control) and Group 2 will receive glibenclamide (5–20 mg/day according to glycemic control) added-on to metformin (500–2550 mg/day according to glycemic control). Blood samples will be collected after 12-h overnight fasting at screening visit and then after 12 weeks of treatment with vildagliptin (Group 1) or glibenclamide (Group 2). Renin-angiotensin system blockers will be prescribed to all subjects at the screening visit and all other antihypertensive drugs will be maintained. Subjects will have three return consultations. The first will be to randomize patients to Group 1 or 2 and they will be evaluated after four and 12 weeks. Compliance will be monitored by pill counts at the second and last visits. The glycemic control will be evaluated by glycated hemoglobin and fasting glucose. Adverse events will be evaluated on the basis of spontaneous reports and interviews by the investigator. Considering side effects and safety, nausea, upper abdominal pain and flatulence are expected, although uncommon, while taking vildagliptin. The most frequent side effect of glibenclamide is hypoglycemic events. Changes in blood count, renal function, and liver function are not expected with either treatment.

Table 2 shows a summary of key practical aspects of the study with all follow-up visits and requested exams.

**Table 2 Tab2:** Key practical aspects of the study with all the clinical visits and the requested exams

Visits	Screening	Visit 1	Visit 2	Visit 3
Weeks	−1	1	4	12
Informed consent	X			
Inclusion and exclusion criteria	X	X		
Medical history	X			
Medical evaluation/physical examination	X	X	X	X
Randomization		X		
Pregnancy test	X			
Creatinine	X			X
Fasting glucose	X		X	X
Ultrasensitive C-reactive protein	X			X
Total cholesterol	X			X
High-density lipoprotein cholesterol	X			X
Triglycerides	X			X
Glycated hemoglobin	X			X
Alanine aminotransferase	X			X
Microalbuminuria	X			X
Ambulatory blood pressure monitoring		X		X
Treadmill test	X			
Determination of the central aortic pressure and vascular stiffness markers		X		X

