## Outcomes and outcome adjudication

Change in the RHI from baseline after 12 weeks of vildagliptin vs. glibenclamide treatment.Change in the central blood pressure from baseline to after 12 weeks of vildagliptin vs. glibenclamide treatment.

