### Statistics

All analysis will be performed using SPSS Statistical Software (IBM SPSS Statistics for Windows, Version 21.0. Armonk, NY: IBM Corp.). Continuous variables will be presented as mean ± SD and categorical variables as frequencies. Differences between the both groups at baseline will be evaluated by unpaired *t* test or the Mann–Whitney test for comparison of continuous variables. The Chi square test or Fisher’s exact test will be employed to compare categorical variables. The change from baseline to 12-weeks follow-up in the both groups will be evaluated using the paired *t* test for continuous variables. Pearson’s correlation will be used to assess the relationship between HbA1c and RHI and AIx, after confirmation of similarity between groups in respect to demographic data (age, gender, GFR, and comorbidities: hypertension and dyslipidemia) and HbA1c targets after 12 weeks of considered treatment. Thus, the Pearson’s correlation obtained will be potentially consequent to distinct therapeutic responses. For all analysis, a 2-sided *P* < 0.05 will be considered statistically significant.

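### The Pearson correlation of HbA1c with RHI and AIx has no treatment term, so it cannot be read as a difference between the drugs, and its similarity condition uses a post-randomisation result

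*Protocol article*

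**What the plan says.** The Outcomes section defines the first outcome as a comparison of arms: "Change in the RHI from baseline after 12 weeks of vildagliptin vs. glibenclamide treatment". The abstract's Results paragraph expects vildagliptin to improve endothelial function "compared to glibenclamide treatment, independently of glycemic control".

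The Statistics section brings HbA1c together with the vascular measures once only. Pearson's correlation "will be used to assess the relationship between HbA1c and RHI and AIx, after confirmation of similarity between groups". The similarity list covers age, gender, GFR, hypertension and dyslipidemia, "and HbA1c targets after 12 weeks of considered treatment". The paragraph then infers that the "correlation obtained will be potentially consequent to distinct therapeutic responses".

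The section names no test or margin for similarity and does not say what happens if the arms differ. It does not say whether the correlation is pooled or by arm, or whether it uses changes or 12-week values. Unpaired tests of continuous variables are tied to baseline ("Differences between the both groups at baseline will be evaluated by unpaired"), and change is tested with a paired test ("The change from baseline to 12-weeks follow-up in the both groups will be evaluated using the paired"). No model holding treatment and HbA1c together is described.

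**The concern.** Three things in the stated text do not fit together.

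- **The inference.** A correlation describes how HbA1c and RHI vary together across patients. It does not compare the drugs. Making the arms alike in HbA1c does not turn it into a comparison; it removes the one route by which treatment could move the coefficient away from zero.
- **The condition.** Twelve-week HbA1c, whether achieved value or target attainment, is a result of the treatments. Under Randomization and follow-up, glibenclamide is given in "mg/day according to glycemic control) added-on to metformin", and metformin is also dosed to glycemic control. If the condition acts as a gate, the analysis is dropped when the arms differ in HbA1c, which is when separating glycemic from other effects matters most.
- **The confirmation.** With 20 to 25 patients per arm, a non-significant difference does not establish similarity.

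At stake is how a secondary result is reported. A correlation could be credited to different drug responses when the drugs do not differ, or a null correlation could be set against a real difference.

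**Working it through.** The plan gives no figure for this analysis, so there is none to reproduce.

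**Inputs from the protocol.** 25 per arm; 20% loss leaves 25 × 0.8 = 20 per arm; two-sided 0.05; SD of RHI 0.3.

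**Assumed inputs.** HbA1c and the outcome each have within-arm SD 1. δ is the arm difference in HbA1c, τ the treatment effect on the outcome, and β the slope on HbA1c. On the protocol's SD, τ = 1 means 0.3 RHI units.

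**Step 1: what the pooled correlation contains.** With equal arms, outcome = τ·arm + β·HbA1c + error, and

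- covariance = β + (δ/4)(τ + βδ)
- variance of HbA1c = 1 + δ²/4
- variance of outcome = 1 + (τ + βδ)²/4

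If the arms are alike in HbA1c (δ = 0), then r = β / √(1 + τ²/4). Treatment appears only in the denominator, so it can only shrink r towards zero:

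- τ = 1, β = 0: r = 0
- τ = 0, β = −0.5: r = −0.50
- τ = 1, β = −0.5: r = −0.5/√1.25 = −0.45

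Within a single arm τ is a constant and drops out altogether.

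**Step 2: simulation** (20,000 runs per row, δ = 0). The last column is the arm coefficient in a linear model of outcome on arm and HbA1c.

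| Per arm | τ | β | Mean r | Pearson p<0.05 | Arm coefficient p<0.05 |
|---|---|---|---|---|---|
| 20 | 1 | 0 | 0.00 | 5% | 86% |
| 20 | 0 | −0.5 | −0.49 | 92% | 5% |
| 20 | 1 | −0.5 | −0.44 | 84% | 94% |
| 25 | 1 | 0 | 0.00 | 5% | 93% |
| 25 | 0 | −0.5 | −0.50 | 97% | 5% |

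The mean r values agree with step 1. The correlation is less often significant when a treatment effect is added to the same slope (84% against 92%).

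**Step 3: what non-significance would confirm.** Assume similarity means p ≥ 0.05 in a two-sample t test on HbA1c. The non-centrality is d√(n/2): for d = 0.5 it is 0.5 × √10 = 1.58 at 20 per arm and 0.5 × √12.5 = 1.77 at 25. The chance of being called similar is:

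| True gap (SD) | 20 per arm | 25 per arm |
|---|---|---|
| 0.3 | 85% | 82% |
| 0.5 | 66% | 59% |
| 0.8 | 31% | 21% |

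Conversely, with five or six independent tests at 0.05 on arms that are truly alike, at least one differs by chance in 1 − 0.95⁵ = 23% or 1 − 0.95⁶ = 26% of trials.

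**Step 4: both together.** With no treatment effect, β = −0.5 and HbA1c 0.5 SD lower in one arm, 66% of trials with 20 per arm pass the t-test condition, and 93% of those give a significant correlation.

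**The case against.** A reader might infer that the trial's main claim rests on this correlation. The documents do not support that. The stated aims concern endothelial function and arterial stiffness, and the outcomes are changes in RHI and central blood pressure by arm. Independence from glycemic control appears as an expected result in the abstract and as mechanism in the discussion. The Statistics section does not tie the correlation to it; that link is an inference, drawn because no other stated analysis relates HbA1c to RHI. Nor does the text gate the RHI comparison itself.

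A reader might also infer that significance tests decide similarity. No test is named, so step 3 illustrates an assumed rule. A strict gate is the natural reading of the text, but not the only one: similarity could be meant as a condition for interpretation. Similar 12-week HbA1c with different RHI would indeed be a sensible argument for independence. That argument comes from comparing RHI between arms, however, and the correlation adds nothing to it.

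The Pearson rates in step 2 are not errors of the correlation as such. Where HbA1c and RHI are truly linked it should be significant, and where they are not it should not be. They become errors only when the coefficient is read as a treatment finding, which is what the concluding sentence invites, although it is hedged by potentially. Correlations by arm or of changes would describe associations within each arm, and still not the difference in RHI between arms.

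Finally, adjusting for HbA1c change also uses a post-randomisation variable. That stands, and it limits what the supportive model can claim.

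**Conclusion.** The point holds as an invalid inference in the stated text, not as an omission that an unseen analysis plan might fill. That the correlation has no treatment term follows from algebra and needs no assumed values. Under the condition of similar HbA1c, a treatment effect can only weaken the coefficient. The similarity condition depends on a result of treatment, and if judged by non-significance it would pass a true 0.5 SD gap in about 66% (20 per arm) or 59% (25 per arm) of trials.

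The simulated rates rest on normal data and on assumed values of τ, β and δ that the protocol does not give. The simulated model also has no unmeasured factor affecting both HbA1c and RHI, so its 86% and 93% are favourable to HbA1c adjustment. The fault lies in a supportive analysis and leaves the outcome definitions untouched. It should be corrected before results are analysed, because the sentence as written could credit the drugs with a correlation that arises with no drug difference at all.

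**What to change.** 1. Delete the similarity condition and the sentence attributing the correlation to different treatment responses. Keep any HbA1c correlation as descriptive only, stating whether it is pooled or by arm and whether it uses changes or 12-week values.
2. Make the between-arm comparison of RHI, adjusted for baseline RHI, the main analysis, run whatever the arms look like on HbA1c.
3. Add a supportive model for RHI and for AIx with treatment, the baseline value and change in HbA1c. Report the treatment coefficient and 95% CI with and without HbA1c change.
4. State that HbA1c change arises after randomisation and is not protected by it, so any claim of independence from glycemic control is exploratory.

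**Cost.** Analysis wording and a little more analysis. Table 2 already schedules HbA1c at screening and week 12, and the vascular tests at visits 1 and 3. The price is a weaker independence claim, which is all this design can support.

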## Results/discussion

The study has started in December 2013 and patient recruitment is programed until October 2015. It is expected that vildagliptin will improve the endothelial function in patients with T2DM and hypertension more than glibenclamide treatment. Hyperglycemia causes endothelial dysfunction because it reduces the bioavailability of endothelium-derived nitric oxide (NO). Although the main action of GLP-1 is to increase glucose-stimulated insulin secretion from pancreatic beta cells, there is also evidence of physiological signaling from GLP-1 in endothelial and vascular smooth muscle cells. Thus, GLP-1 has vasodilator actions mediated by a specific GLP-1 receptor in the vascular endothelium and may improve endothelial function in animals and humans [15–17], independently of its effect on glycemic control.

Arterial stiffness is recognized as another cardiovascular risk marker [32]. Patients with both HT and DM exhibit higher arterial stiffness compared to those with either DM or HT alone [33]. Applanation tonometry estimates arterial compliance and the central blood pressure and is used to assess arterial stiffness [42, 43]. Evidence shows that the central blood pressure is more relevant to cardiovascular outcomes than the peripheral BP [44–46]. On the other hand, Endo-PAT, a non-invasive method, evaluates the vascular vasodilator propriety and, consequently, endothelial function. Both hypoglycemic drugs, vildagliptin and glibenclamide, may improve glycemic control. However, only vildagliptin and other DPP-4 inhibitors have provided beneficial effects of the endothelium [22, 23].

## Conclusions

This study will evaluate the effect of vildagliptin compared to glibenclamide, both added-on to metformin, on endothelial function and arterial stiffness in type 2 diabetic patients with hypertension. The improvement of endothelial function will demonstrate that DPP-4 inhibitors could improve cardiovascular outcome, especially in high cardiovascular risk patients.

## Abbreviations

ABPM: ambulatory blood pressure monitoring
ADMA: asymmetric dimethylarginin
AIx: *augmentation index*
BMI: body mass index
BP: blood pressure
CAD: coronary artery disease
CRP: C-reactive protein
CVD: cardiovascular disease
DBP: diastolic blood pressure
T2DM: type 2 diabetes mellitus
DPP-4: dipeptidyl peptidase-4
FMD: flow-mediated vasodilatation
GIP: glucose-dependent insulinotropic polypeptide
GFR: glomerular filtration ratio
GLP-1: glucagon-like peptide 1
HDLc: High-density lipoprotein cholesterol
HT: hypertension
LDLc: Low-density lipoprotein cholesterol
MDRD: Modification of Diet in Renal Disease
PAI-1: plasminogen activator inhibitor 1
PAT: peripheral arterial tonometry
PWV: pulse wave velocity
RHI: reactive hyperemia index
SBP: systolic blood pressure
SD: standard deviation
TC: total cholesterol
TG: triglycerides
UACR: urinary albumin-to-creatinine ratio
